## Abstract

**Background:**

As an alternative to hospital admission, crisis resolution teams (CRTs) provide intensive home treatment to people experiencing mental health crises. Trial evidence supports the effectiveness of the CRT model, but research suggests that the anticipated reductions in inpatient admissions and increased user satisfaction with acute care have been less than hoped for following the scaling up of CRTs nationally in England, as mandated by the National Health Service (NHS) Plan in 2000. The organisation and service delivery of the CRTs vary substantially. This may reflect the lack of a fully specified CRT model and the resources to enhance team model fidelity and to improve service quality. We will evaluate the impact of a CRT service improvement programme over a 1-year period on the service users’ experiences of care, service use, staff well-being, and team model fidelity.

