The US National Implementing Evidence-Based Practices Project (EBP) [28, 29] offers a model for evaluating and promoting quality improvement in complex service-level mental health interventions. Integral elements of the EBP approach are service reviews using a fidelity measure that assesses how far services are achieving a model of good practice and utilisation of a resource kit to support implementation and quality improvement [30]. Resource kits typically consist of guidance, training materials, and coaching and support for service managers and staff, designed to help services address areas where high model fidelity has not been achieved. Modelling of factors associated with successful implementation of evidence-based practices has helped to theoretically underpin the EBP implementation model [31, 32]. Attention to workforce development and training may in itself be insufficient to achieve high fidelity implementation of complex mental health interventions: securing leadership support, organising workflow (service structures and organisation) to support implementation, and providing feedback to reinforce implementation successes are also required [31]. Access to technical assistance that enables understanding of the specific requirements of a complex intervention can also facilitate implementation [32]. The EBP programme has successfully developed fidelity scales and implementation resources for a range of service-level interventions including supported employment [33] and assertive community treatment [34]. Previous studies have found correlations between fidelity to an evidence-based practice and better client outcomes [35, 36]. CRTs are comparable with models in the EBP project because trial evidence exists for their efficacy in the right conditions. A CRT fidelity scale was developed in an earlier part of this programme of research (The CORE Study) [37]. This trial will test the effectiveness of the CORE CRT Service Improvement Programme in helping CRTs improve outcomes and achieve high model fidelity.

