## Aims

This trial tests the CORE CRT Service Improvement Programme in a cluster-randomised trial. CRTs randomised to the intervention arm will receive the Service Improvement Programme over a 1-year period, and control CRTs will not receive the intervention. The study aims to investigate whether a CRT Service Improvement Programme can improve service users’ experience of CRT care, reduce acute service use, and improve CRT staff well-being. The primary outcome is service user satisfaction, measured using The Client Satisfaction Questionnaire (CSQ-8) [38]. We will also explore whether the fidelity scores of the CRT teams receiving the Service Improvement Programme rise over the 1-year intervention period and the associations between team fidelity score and service outcomes. Through a qualitative and process evaluation, we will seek to understand stakeholder experience of the CRT Service Improvement Programme, contextual factors constituting barriers and facilitators to its implementation, and any mechanisms by which it may improve team effectiveness.

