## The intervention

The CORE CRT Service Improvement Programme is designed to support teams to identify target areas for service improvement and to produce and implement plans that improve current practice. Structures and resources included in the Service Improvement Programme are available in the online CRT Resource Pack. They include the following:Assessment of adherence to current CRT best practice measured by the CORE CRT fidelity scale. Fidelity reviews will be conducted at baseline and at the end of the 12-month study period with control teams and intervention teams. Intervention teams will receive an additional 6-month review, with feedback from the external reviewers being included on the resulting fidelity report to the CRT manager and team. Intervention teams will be offered a meeting with the reviewers to discuss their 6-month report. This will be used to identify targets for service improvement and planning for how to achieve them and to provide positive reinforcement of any implementation successes achieved during the previous 6 months.Structures to guide service improvement work. A number of structures based on an EBP framework will be utilised to guide service improvement. These structures include a 1-day, whole-team scoping event for each CRT to kick start the Service Improvement Programme and feedback on the fidelity review; service improvement groups (SIGs) of managers and clinical leaders within each CRT meeting regularly to develop service improvement plans (SIPs); and collaboration between CRT managers and staff in teams receiving the intervention, which will be promoted by the research team. Collaboration activities will include an online forum; regular bulletins from the research team about implementation progress at study sites; and at least two meetings/events during the study period to promote sharing of experience, knowledge, and best practice. Evidence suggests that these types of collaborative learning events have the potential to support improvements in the quality of services [42].A local facilitator. Participating NHS Trusts will fund a local facilitator with dedicated time (0.1 full time equivalent for each intervention team) to help teams implement the Service Improvement Programme by encouraging the use of the resource pack; discussion and coaching of the CRT manager; mentoring, supervision, and training of the CRT staff; and liaison with senior Trust management regarding resources or organisational support required to achieve model fidelity. The local facilitator may either be an employee of the participating NHS Trust or an external consultant identified by the study team, depending on local resources and preferences. The facilitator will typically be a manager or senior clinician with experience of working in or with CRTs. Facilitators will be provided with initial and follow-up group training and individual coaching at least once a month by appropriately experienced members of the research study team (a clinical psychologist with CRT clinical experience and a clinical and academic psychologist with expertise in leadership and change management in mental health service contexts). Facilitators will be invited to regular implementation meetings with the study team to offer feedback on how the intervention is progressing and discuss ways of overcoming barriers to service improvement.Access to a web-based resource pack manual, including practical resources, guidance, and training materials to support implementation; case studies from high fidelity CRT services outlining strategies for achieving high fidelity; relevant reading; useful links; video and audio clips of service users, carers, and staff involved in clinical CRT work; and service improvement research providing rationale for fidelity scale items and ideas for improving support. An outline of the structures designed to help facilitate service improvement over the 1-year intervention will also be included.

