### 4. Qualitative and process evaluation

#### Fidelity reviews

CRT model fidelity will be assessed in all teams at baseline and 1-year follow-up using the CORE CRT Fidelity Scale [37], a 39-item measure yielding a total score ranging from 39–95.

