### 4) Qualitative and process evaluation

#### Process data

Fidelity reviews: We will provide descriptive data regarding changes in the team fidelity scores over the 1-year study period. We will explore the extent to which team fidelity score can explain variations in individual satisfaction with care. This analysis will use linear random effects modelling, with a random effect for CRT.Descriptive data on the number of implementation activities at each site and the proportion of total implementation activities of each type will be reported for each CRT team.We will also report whether the following implementation structures recommended as part of the Service Improvement Programme were achieved at each intervention CRT: scoping day; development of a service improvement plan; formation of a service improvement group; whether the SIG met at least six times during the study; attendance of team/Trust representatives at a learning collaborative day.For all 25 teams, we will report whether any other major service improvement initiatives took place during the study intervention year.The online resource kit used by the CRT staff will be monitored via Google Analytics, which captures time spent on individual pages and document downloads.

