## Research implications

The main trial results will provide preliminary evidence regarding whether the CORE CRT Service Improvement Programme is effective in increasing model fidelity and improving outcomes in CRTs. The study will also provide the following:Evidence regarding the validity of the CORE CRT fidelity scale. We will explore, through multilevel modelling, whether team fidelity scores relate to important service user and staff outcomes.Evidence regarding the feasibility of implementing the intervention from process data and barriers and facilitators to implementation from the qualitative evaluation, which can help understand any mechanisms of change and inform future implementation programmes.

Implementation represents the biggest challenge to translating research knowledge into patient benefit [52]. CRTs exemplify this challenge: trial evidence suggests they can be effective in reducing admissions and enhancing service user experience, but observational studies and audits indicate the benefits of CRT implementation on a national scale may be smaller and less consistent than originally expected [19, 20]. Means of supporting the effective implementation of the CRT model are therefore of high interest to service planners. Through testing a theoretically underpinned, clearly defined, extensive package of implementation resources for CRTs, our trial can provide evidence to address this important issue.

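### The article promises evidence that the programme raises model fidelity, but commits only to describing change and names no between-arm estimate, so change shared by both arms could be read as a programme effect

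*Protocol article*

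**What the plan says.** Three places in the protocol article set a causal goal for fidelity.

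- The Abstract (Background) says the trial will evaluate the programme's impact "on the service users’ experiences of care, service use, staff well-being, and team model fidelity".
- The main Background says the trial will test the programme's effectiveness "in helping CRTs improve outcomes and achieve high model fidelity".
- Research implications says the main results will give preliminary evidence on "whether the CORE CRT Service Improvement Programme is effective in increasing model fidelity and improving outcomes in CRTs".

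The operational text is narrower. The Aims section will explore "whether the fidelity scores of the CRT teams receiving the Service Improvement Programme rise over the 1-year intervention period", without mentioning control teams. Under Analysis, Process data, the commitment is: "We will provide descriptive data regarding changes in the team fidelity scores over the 1-year study period". The only model named for fidelity uses it as a predictor: "We will explore the extent to which team fidelity score can explain variations in individual satisfaction with care".

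Fidelity is measured in both arms. The Measures section states that "CRT model fidelity will be assessed in all teams at baseline and 1-year follow-up", and the intervention section that "Fidelity reviews will be conducted at baseline and at the end of the 12-month study period with control teams and intervention teams". The Randomisation section places the baseline reviews of all teams in a Trust before that Trust's teams are randomised.

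**The concern.** A rise among the programme teams mixes the programme's effect with anything else that moved scores that year. The article itself names candidates. Control teams also get a baseline review and written report (The intervention). Other major improvement initiatives are anticipated and will be recorded in all 25 teams (Process data). Improving acute mental health care is described as a national policy priority (Background).

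Fidelity is what the programme acts on most directly. If the conclusion about it rests on within-arm change, a shared rise could be mistaken for benefit. Equally, a flat score in programme teams could hide a benefit if control teams declined. Randomisation supplies the comparison that separates these cases, and the article does not commit to using it for this measure.

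**Working it through.** **1. Claim, question and analysis side by side**

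| Element | Section | Content |
|---|---|---|
| Claim | Abstract; Background; Research implications | Effect of the programme on fidelity |
| Question | Aims | Do programme teams' scores rise? |
| Analysis | Process data | Descriptive change; no arm contrast named |
| Data | Randomisation; The intervention; Measures | Pre-randomisation and 12-month scores, 15 + 10 teams |

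The Analysis section does describe comparisons between arms for satisfaction and continuity of care, for service use, and for staff outcomes. Fidelity is the exception.

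**2. What each quantity estimates**

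Let *s* be the mean change over the year that would occur in either arm without the programme, and *p* the programme's effect.

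- Expected change in programme teams: *s* + *p*
- Expected change in control teams: *s*
- Expected difference between arms: (*s* + *p*) − *s* = *p*

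The question worded in the Aims concerns *s* + *p*, while the promised conclusion concerns *p*. As an illustration only, with *p* = 0 and a shared rise of *s* = 0.5 SD, programme teams rise by 0.5 SD on average and the between-arm difference averages 0.

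**3. Precision of the between-arm estimate**

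The article gives no figure for fidelity to reproduce; its power statement concerns the satisfaction score only. It also gives no SD for the fidelity score and no correlation *r* between baseline and follow-up. Results are therefore in between-team SD units, with *r* assumed to be 0.3, 0.5 or 0.7.

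Inputs from the article: 15 programme teams, 10 control teams, eight Trusts (Abstract).

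Residual df for a regression on arm, baseline score and Trust: 25 − (1 intercept + 1 arm + 1 baseline + 7 Trust terms) = 25 − 10 = 15. The two-sided 95% critical value is t(15) = 2.131.

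Standard error = √(1 − *r*²) × √(1/15 + 1/10), where √(1/15 + 1/10) = 0.408. Half-width = 2.131 × SE. The difference detectable with 80% power at two-sided 5% comes from the noncentral t distribution on 15 df with noncentrality (difference ÷ SE).

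| *r* (assumed) | √(1 − *r*²) | SE | 95% CI half-width | Detectable, 80% power |
|---|---|---|---|---|
| 0.3 | 0.954 | 0.389 | 0.83 SD | 1.17 SD |
| 0.5 | 0.866 | 0.354 | 0.75 SD | 1.06 SD |
| 0.7 | 0.714 | 0.292 | 0.62 SD | 0.87 SD |

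Without the Trust terms (22 df, t = 2.074) the half-widths are 0.81, 0.73 and 0.60 SD, so the degrees of freedom spent on Trust cost little. Two things are left out: precision lost to uneven arm splits within Trusts, and precision gained if Trust explains variance in the score.

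**The case against.** The strongest reply is that the descriptive sentence is not limited to programme teams. Control teams are scored at both times, and describing change in a two-arm trial usually means showing it by arm, which would make a shared drift visible. This stands. A reader might infer that shared drift will be credited to the programme, or that the control scores will go unused; the article supports neither. It supports only that such misreading is possible, because no contrast is specified.

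Second, fidelity sits under the process evaluation, the aim is worded as exploratory, and Research implications promises preliminary evidence only. This lowers the stakes. But preliminary evidence of effectiveness still concerns *p*, and within-arm change does not isolate it.

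Third, the Abstract says outcomes will be compared between arms. That sentence follows the one on adherence, so it is ambiguous. Fidelity is, however, outside the Abstract's list of primary and secondary outcomes, adjustment for participant characteristics does not fit a team-level score, and the Analysis section gives fidelity no such comparison.

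Fourth, modelling detail often belongs in an analysis plan or full protocol, neither of which is shown. That would answer a complaint about missing detail. Here the article states a descriptive method and a within-arm question alongside an effectiveness claim, and these do not match.

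The planned interviews with control managers and the record of other initiatives help interpretation but do not replace an estimate.

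**Conclusion.** The point holds as a mismatch between the promised conclusion and the stated question and analysis. No between-arm fidelity estimate is committed to, although the randomised data for one will exist, and shared change could be read as a programme effect.

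The size of any shared change cannot be derived from the article. A reader might want to attach a false-positive rate by testing the rise within the 15 programme teams. No such test is planned, so no such rate applies to this trial.

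The between-arm estimate would be imprecise: about ±0.62 to ±0.83 SD, with detectable differences of about 0.9 to 1.2 SD, given correlations of 0.7 down to 0.3 and the simplifications stated above. It nevertheless addresses the question asked, which within-arm change does not at any precision. It would not remove bias from fidelity reviews made with knowledge of allocation; the article makes no arrangements for blinding. The satisfaction, service-use and staff comparisons are unaffected. The change should be made, but it does not threaten the trial's main result.

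**What to change.** - **Analysis, Process data:** add that the 12-month total fidelity score will be compared between randomised arms in all 25 teams by linear regression on arm, baseline fidelity score and Trust, reporting the adjusted mean difference and 95% confidence interval. Keep the descriptive changes as a supplement, shown for both arms.
- **Aims:** ask whether scores rise more in programme teams than in control teams.
- **Research implications:** base the statement about increasing fidelity on that adjusted difference, and present it as an estimate with its interval.

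The cost is one regression on scores already planned for every team, plus wording. The drawback is the wide interval: an interval that includes zero should not be reported as showing no effect on fidelity.

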#### Staff focus groups

Qualitative data from interviews with local facilitators and focus groups with staff from CRTs implementing the resource kit will be analysed using thematic analysis [49] aided by qualitative analysis software (Nvivo9). Thematic analysis will allow exploration of themes relating directly to our research questions and arising more inductively from the data. Analyses will be conducted collaboratively by a group of researchers within the team to enhance the validity of the analysis.

### Dissemination and access to trial results

The trial findings will be publicly available via a final report to the study funder, the National Institute for Health Research. The trial will also be reported in peer-reviewed journals. Information regarding the study, including the trial protocol, are available through the study website [50], and the web-based resource pack is now publicly available [51].

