
The CORE CRT Service Improvement Programme, with ongoing implementation support from facilitators during the year of the intervention, will thus provide ongoing help to teams during the course of the project in securing leadership support, structuring team workflows to support implementation, and providing expert technical assistance with implementing the CRT model where required, in line with EBP implementation theory [31]. Services in the control group will receive a fidelity review and written report at baseline and at the end of the study period but no other implementation support. Control teams will not be provided with details of the online resource pack; teams within the intervention group will undertake not to share resources or promote service improvement in the control teams until the end of the trial.

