### Limitations

Limitations of the study relate to the following:Blinding: Due to the need for researchers to have ongoing contact with CRT teams and facilitators throughout the intervention, it will not be possible for researchers to be blinded to team randomisation, and this approach could lead to researcher bias.Contamination: As NHS Trusts often try to ensure their services are operating in a consistent way, a limitation of the study is the potential for contamination between teams receiving the Service Improvement Programme and control teams within the same Trust. To minimise this, researchers will ensure teams are informed that for the clarity of study findings it is beneficial if any CORE-related service improvement work is limited to the intervention teams until the end of the study, and this includes limiting access to the online resource kit. In addition, monitoring of contamination through interviewing control team managers will serve to highlight the extent of this.Retrospective collection of some data: It will not be feasible to complete all baseline data collection before randomisation. However, all staff data will be collected before the scoping day – the kick-off, one-day team meeting in each CRT which is arranged as soon as possible after the start of the intervention year, and service user data will be collected from service users discharged before the scoping day. Due to the nature of the service user sample, different service users will be participating at baseline and follow-up.

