### Trial status

The recruitment of service user and staff participants for outcome evaluation and the trial intervention are ongoing at the time of submission of this protocol for publication. The final report of the study to the funders is due for submission by April 2017.

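### The resource pack to be withheld from control teams is described as already public, with no release date and with the intervention reported as ongoing at submission

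*Protocol article*

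**What the plan says.** The intervention lists four groups of components: fidelity review with feedback, structures to guide improvement work, a local facilitator, and the online pack, described as "Access to a web-based resource pack manual, including practical resources, guidance, and training materials to support implementation". For the control arm the same section says "Control teams will not be provided with details of the online resource pack", and that intervention teams "will undertake not to share resources or promote service improvement in the control teams until the end of the trial".

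Limitations recognises contamination between teams in one Trust. Its stated response is to tell teams that programme-related work is best confined to the intervention arm until the study ends, and "this includes limiting access to the online resource kit". Randomisation is stratified by Trust, so that each Trust holds teams of both arms.

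Dissemination and access to trial results says that "the web-based resource pack is now publicly available" and gives a reference for it. Trial status says that outcome recruitment and "the trial intervention are ongoing at the time of submission of this protocol for publication".

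On pack use, the Process data part of the Analysis says: "The online resource kit used by the CRT staff will be monitored via Google Analytics, which captures time spent on individual pages and document downloads". Process monitoring, under Procedures, names the same tool. Neither place mentions a login or a team identifier.

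**The concern.** The contrast between arms depends partly on control teams not having the pack. If the site is open while the intervention year runs, that part of the control condition rests on goodwill and on control staff not looking. They have some reason to look: teams know their allocation, control teams receive a written fidelity report at baseline, and Limitations itself notes that Trusts try to run their services consistently. Use of the pack by control teams would pull the arms together on satisfaction (the primary outcome) and on model fidelity.

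The second issue does not depend on any control team opening the site. Page time and downloads on a public website mix intervention staff, control staff, other services and general readers, so the planned description of pack use by CRT staff would be inflated by an unknown amount.

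**Working it through.** **Setting the statements side by side**

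1. Limitations: access to the kit is to be limited until the end of the study. Public availability before that point conflicts with this directly.
2. The intervention: control teams are not given details of the pack. Read literally, this can survive an open site, because nobody need hand over the details. Its purpose is undercut but its wording is not breached.
3. Dissemination: the pack is public now. No date is attached.
4. Trial status: the intervention was ongoing at submission. This has a reference point, but not necessarily the same one as item 3.
5. Procedures: each Trust's intervention year starts when its facilitator takes up post. Any overlap with the open period could therefore differ between Trusts.

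Items 1 and 3 can be reconciled only if the pack was opened after the last Trust's follow-up ended. The article does not say so, and item 4 points the other way.

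**Analytics**

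The stated target is use by CRT staff, and the stated instrument is site-wide Google Analytics. On an open site with no described means of separating visitors, the total is use by everyone. It cannot be divided by arm or by team.

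**Size of a possible dilution (illustration only)**

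Inputs from Sample size: 15 and 10 teams of 15 (225 and 150 participants), SD 7.0, ICC 0.05, difference 3.5 points. The section does not state alpha; two-sided 5% is assumed.

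- Design effect = 1 + (15 − 1) × 0.05 = 1.70.
- Standard error = 7 × √1.70 × √(1/150 + 1/225) = 0.962 points, or 0.137 SD.
- Plan's own figure: 3.5 / 0.962 = 3.64, and 3.64 − 1.96 = 1.68, which gives power of 95.3%. With a t distribution on 25 − 2 = 23 degrees of freedom it is 93.6%. The plan states 97%. The normal figure is within two percentage points of that, and the point here does not turn on the gap.

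The documents give no uptake or dilution figure. Suppose control teams gain a share c of the effect, so that the observed contrast is 3.5 × (1 − c):

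| c (assumed) | Contrast, points | Power, normal | Power, t on 23 df |
|---|---|---|---|
| 0 | 3.50 | 95.3% | 93.6% |
| 0.1 | 3.15 | 90.6% | 88.0% |
| 0.2 | 2.80 | 82.9% | 79.6% |
| 0.3 | 2.45 | 72.1% | 68.4% |

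The two methods show the same pattern. The table says what a given dilution would cost, not which dilution to expect.

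**The case against.** The strongest reply is that the overlap is inferred. One statement says now, the other refers to submission, and text can be updated between submission and publication. That stands: the article does not prove that the pack was open during any Trust's intervention year. It also gives no release date that would rule this out.

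Second, the Limitations passage can be read as a request to teams rather than a promise of a technical lock. That is a fair reading, but a request to limit access is much weakened when the site is open and the article cites where to find it.

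Third, contamination is disclosed and monitored. Control managers are contacted at 6 and 12 months, and control teams have fidelity reviews at baseline and at the end. This stands in part. These steps would help show whether control practice moved, but they detect use rather than prevent it, and the calls depend on managers knowing what their staff viewed.

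Fourth, web usage is a descriptive process item that feeds no stated hypothesis test, and the full protocol may hold operational detail. That limits the weight of the analytics point. It does not make open-site totals interpretable as CRT staff use.

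A reader might go further and infer that the control arm was contaminated, that a null result would be uninterpretable, or that power will fall to the figures tabulated. The documents support none of these. They report no control-team use and do not say that the control fidelity report mentions the pack. The facilitator, scoping day, improvement groups and 6-month review are unaffected by web access, and the background cites theory that training alone may be insufficient.

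**Conclusion.** The concern holds in limited form. The article states a safeguard, limited access to the kit until the study ends, and also states that the kit is public, while describing the intervention as ongoing at submission. As written, the plan undercuts its own control condition in a design where both arms share Trusts. Overlap with the intervention year is the natural reading, not an established fact. Actual use by control teams is not shown. Because the pack is one of four components, any loss of contrast would be partial, and its size is unknown; the 10% to 30% shares are assumptions, as is the two-sided 5% level.

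The conclusion on web analytics needs only that the site is open and that no other means of separating visitors exists; the article describes none. It is worth correcting promptly, since access can be restricted to useful effect only while follow-up is still under way.

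**What to change.** - Put the pack behind a login issued by team to intervention teams and facilitators only, until month-12 outcomes have been collected in the last Trust. Amend the Dissemination statement to say that public release follows that point.
- Count pack use by team login instead of by site-wide Google Analytics.
- For any period when the site was open, give the dates against each Trust's intervention year. A login cannot undo exposure that has already happened, so this record is needed in any case.
- In the control-manager calls already planned at 6 and 12 months, ask explicitly whether staff used the pack. Report the number of exposed control teams beside the primary result.

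The cost is a login on an existing website, a short protocol change and one added question in calls that will be made anyway. The downside is that services outside the trial wait some months for public access.
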